### Intervention

#### Usual care

This will be received by both control and intervention groups.

In the inpatient setting, all participants will be seen by a physiotherapist a minimum of daily on weekdays and will follow their hospital’s standard postoperative pathway. Average hospital length of stay for people after THR and TKR is 5 days.^1^ Rehabilitation consists of gait re-education, exercises and advice regarding transferring from bed to chair, toileting and dressing. Advice on continuation of gait progression and activities of daily living are encouraged by the physiotherapy team. Once considered medically fit and safe by the multidisciplinary team, patients are discharged. These follow current, routine, nationwide practice.^23^

All participants attend six weekly, 30 min group-based exercise classes within each hospital trust’s physiotherapy department after THR or TKR. These groups consist of up to 12 people and commence within 4 weeks post-randomisation. The principles regarding prescription of group exercises to increase range of motion, strength and gait pattern are consistent. While the rehabilitation of THR and TKR focusses on overall lower limb function, all participants following a THR focus on hip exercises, whereas those following a TKR focus on knee exercises. For this trial, exercise diaries will be provided and maintained by participants to monitor exercise performance and compliance within and outside the exercise groups for the 6-week intervention period.

#### Experimental intervention

Participants randomised to the experimental group will receive the same in-hospital care and physiotherapy prior to hospital discharge. They will also receive the same six weekly, group-based 30 min exercise session. The only difference between the two groups is the addition of a 30 min group-based (up to 12 people) behaviour change approach intervention prior to the routine 30 min of exercise and three telephone follow-up calls 2, 4 and 6 weeks after the last group-based session (the PEP-TALK intervention).

The PEP-TALK intervention is theoretically-based within the cognitive-behavioural model of understanding. It uses evidence-based behaviour change techniques to target internal (cognitions and behaviours regarding physical activity) and external factors (social and environmental barriers). It specifically aims to target self-efficacy beliefs and fear-avoidant behaviours. A senior health psychologist (BF), physiotherapist/cognitive-behavioural therapist (ZH) and senior clinical academic physiotherapist (TS) developed an in-person, 1 day training session. The training was delivered by BF and TS to all physiotherapists in the trial who were delegated to deliver the PEP-TALK intervention. The training included role-play, knowledge and understanding testing and supplementary materials to support on-going learning. All physiotherapists were invited to contact the training team (BF, ZH and TS) to clarify any training queries throughout the trial.

In the PEP-TALK sessions, through group discussion, participants and physiotherapists will be encouraged to develop a positive therapeutic alliance, where the physiotherapist will generate an environment of trust and belief around individual challenges participant’s have, to support them to overcome these for sustained physical activity adoption. A treatment log will be completed by the physiotherapists to record the components of what is discussed across the group in each session.

The PEP-TALK intervention also includes a home-practice element. Participants will be supported with skills developed in the group, to work at home on challenges, barriers and facilitators to physical activity behaviour. The ‘home-work’ workbook aims to translate and develop the skills learnt within the group session into daily life activities. The workbook is designed to be used during the six sessions although participants are encouraged to keep this as a record and prompt for long-term behaviour change. The workbook will be referred to in the telephone follow-up calls. The workbook encourages reflective activities such as recording physical, emotional and cognitive barriers and facilitators to physical activity. It also offers problem-solving techniques such as “can you break down a large physical activity (eg, ‘getting the house all cleaned for the family coming over’) into tasks which you can ‘prioritise’, ‘plan’, ‘tolerance level’ and ‘evaluate.’” The workbook also includes other activities to encourage pacing and behaviour modification, goal-setting to the individual’s health and social needs and techniques to challenge fear-avoidant behaviours. Education on exercise and the detrimental effects of physical inactivity will also be discussed. Participants will complete this with their home exercise plan which solely focusses on lower limb exercises rather than their behaviours and thoughts around physical activity.

The same trained physiotherapists who deliver the PEP-TALK intervention will, once the participant has completed their group sessions, deliver three, 20 min telephone follow-up calls. These will occur at 2, 4 and 6 weeks after completing the group sessions. During these follow-up telephone calls, participant’s goals will be reviewed, any barriers to the completion of these goals will be identified and the physiotherapist will review any ‘unhelpful’ and ‘helpful’ thoughts or feelings towards physical activity which may have arisen since the last consultation. Each telephone call will close with the development of longer-term physical activity goal-setting and promotion of empowerment towards physical activity participation using the behavioural principles instilled during the group intervention. A log will be collected by the physiotherapist to record the components of what is discussed during the telephone calls.

#### Delivery

Both the PEP-TALK intervention and exercise groups will be delivered as ‘rolling’ programmes. This means that new participants can join the group as it runs rather than waiting for a new ‘block’ of sessions to start. This will allow greater flexibility in allocating participants to join group sessions, while also avoiding a delay between postoperative referral and starting the sessions. The flexible nature of the experimental intervention also makes this feasible, with no ordering of the content of intervention sessions which would preclude such a rolling programme.

#### Contamination

The physiotherapists who deliver the behaviour change sessions will be taught the skills required to deliver the experimental intervention. These physiotherapists will not be permitted to deliver the control exercise group intervention during the trial period (and vice versa). This approach mitigates the risk of contamination. Due to the interventions being delivered in an outpatient setting, there is a reduced risk of participants sharing their knowledge and experience of the interventions between the control and intervention groups, further minimising the risk of between-group contamination. Participants in the control group will not be permitted to join the experimental intervention group’s exercise sessions (and vice versa). This will also reduce the risk of between-group contamination.

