### Data analysis

#### Sample size

Originally, 250 participants (125 per arm) are required to detect a standardised effect size of 0.4 with 80% power and 5% (two-sided) significance, and allowing for 20% loss to follow-up. These calculations are based on the primary outcome, UCLA Activity Scale, at 12 months, assuming a baseline SD of 2.5 and a between-group difference of 1.^33^ The minimally clinically important difference has been reported as a within person difference of 0.92 points.^33^

The sample size was increased to 260 to account for the amendment in randomisation procedure from 1:1 to 2:1 group allocation, as described earlier.

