#### Statistical analysis

A detailed statistical analysis plan (SAP) will be drafted early in the trial and will be finalised prior to any primary outcome analysis. This will be reviewed and will receive input from the Trial Steering Committee (TSC) and the DSMC.

All analyses will be undertaken on the intent-to-treat population, that is, patients will be analysed as they were randomised regardless of the treatment received. Sensitivity analyses will be undertaken on the per-protocol population to assess a range of potential biasses that could have resulted from loss to follow-up, protocol deviations and withdrawal (including mortality). Numerical and graphical summaries of all data will be presented including descriptions of missing data at each level.

Estimates of treatment effects will be reported with 95% CIs. The primary outcome measure, UCLA Activity Scale at 12 months post-randomisation, will be analysed using a mixed effects linear regression model adjusted for baseline activity, 6 month time point and the stratification factors. Centre will be included as a random-effect to take account of their potential heterogeneity and type of operation, comorbidity index and other time points (baseline and 6 months) will be included as fixed-effects. Treatment by 6 month time point interaction will also be included in the model to allow time specific treatment effects to be calculated The adjusted difference in the means with corresponding 95% CI will be reported together with the mean and 95% CIs for each treatment group. If not normally distributed, then transformation to normality will be considered. If this is not possible, non-parametric techniques (for example Mann-Whitney or Kruskal-Wallis test) will be used with no adjustment. Consistency of any observed intervention effect will be explored using forest plots for various subgroups including site, type of operation (TKR and THR) and comorbidity index using interactions. No formal testing of interaction effects will be undertaken as the trial is not powered to detect these and the effect of the intervention is expected to be similar in the THR and TKR subgroups, although their baseline physical activity may be different, which will be taken into account in the analysis.

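### Physiotherapists and groups are kept to one arm, but the primary model's only random effect is centre, so the CI is too narrow if there is any physiotherapist or group clustering

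*Protocol article*

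**What the plan says.** The Usual care and Experimental intervention sections describe group delivery in both arms, with up to 12 people per group. The experimental physiotherapists also make the three follow-up calls. Under Contamination, staff who deliver the behaviour-change sessions are kept out of the control classes, and the reverse: "These physiotherapists will not be permitted to deliver the control exercise group intervention during the trial period (and vice versa". Participants may not attend the other arm's exercise sessions either.

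The Sample size section states: "Originally, 250 participants (125 per arm) are required to detect a standardised effect size of 0.4 with 80% power". It continues with "allowing for 20% loss to follow-up" and "assuming a baseline SD of 2.5 and a between-group difference of 1". It gives no ICC, cluster size or design effect. The later increase has one stated reason: "The sample size was increased to 260 to account for the amendment in randomisation procedure from 1:1 to 2:1 group allocation".

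For the primary outcome, the Statistical analysis section specifies a linear mixed model: "Centre will be included as a random-effect to take account of their potential heterogeneity". Operation type, comorbidity index, baseline and 6-month time points are fixed effects. No physiotherapist, group or random site-by-arm term is named. Site reappears only in subgroup forest plots, without formal testing.

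**The concern.** Because physiotherapists and sessions do not cross arms, the treatment difference at a site also contains the difference between that site's experimental and control physiotherapists and groups. The centre effect is common to both arms and cancels from that difference, so the model in effect treats participants as independent given centre.

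The protocol itself treats group and therapist as active ingredients. It changed the allocation ratio because experimental groups were too small, counts sessions towards compliance only with at least three people present, relies on a therapeutic alliance, and monitors each physiotherapist. At stake are the coverage of the primary CI, the 5% error rate and the meaning of the stated 80% power. The same model form is carried over to the continuous secondary outcomes.

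**Working it through.** **1. Reproduce the plan's sample size.** Inputs from the Sample size section: difference 1, SD 2.5 (d = 0.4), 80% power, two-sided 5%, 20% loss.
- Normal formula: n per arm = 2(1.96 + 0.8416)² / 0.4² = 98.1, so 99. The exact t-test needs 100.
- 100 / 0.8 = 125 per arm, or 250 in total, as stated.
- For 260, the randomisation section gives 75 at 1:1, then 2:1. Experimental: 37.5 + 185 × 2/3 = 160.8. Control: 37.5 + 185/3 = 99.2. After 20% loss: 128.7 and 79.3.
- SE = 2.5 × √(1/79.3 + 1/128.7) = 0.357. Power = Φ(1/0.357 − 1.96) = 80.0%.

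Both totals reproduce with independent participants, which leaves no margin for clustering.

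**2. Why centre does not help.** Write the outcome as centre effect + treatment effect + physiotherapist/group effect u + individual error. Subtracting arms within a site removes the centre effect but leaves u(experimental) − u(control). With S sites and k physiotherapists per arm per site, this adds about 2 × ICC × SD² / (S × k) to the variance of the estimate.

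Example with ICC 0.05, S = 8, k = 1: 0.95 × 6.25 × (1/79.3 + 1/128.7) = 0.121, plus 2 × 0.05 × 6.25 / 8 = 0.078. The total is 0.199, so SE = 0.446 and power = Φ(1/0.446 − 1.96) = 61%.

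**3. Range for power.** ICC and k are assumptions, as the protocol gives neither. The per-arm design effect is 1 + (m − 1) × ICC, where m is analysed participants per physiotherapist. There are 8 sites and no baseline adjustment.

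| Physiotherapists per arm per site | m (control / experimental) | Overall design effect, ICC 0.01 to 0.05 | Power, ICC 0.01 to 0.05 |
|---|---|---|---|
| 1 | 9.9 / 16.1 | 1.11 to 1.56 | 76% to 61% |
| 2 | 5.0 / 8.0 | 1.05 to 1.26 | 78% to about 70% |
| 3 | 3.3 / 5.4 | 1.03 to 1.15 | 79% to 74% |

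At ICC 0 every row is 80.0%. The abstract gives eight sites and the Trial design section nine; with nine and k = 1 the power range is 76% to 63%.

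**4. Range for type I error.** These are simulations with 8 sites, 10 control and 16 experimental participants per site, a REML fit with a centre intercept only, and a 1.96 critical value. The covariates were left out for simplicity. Repeated runs differ by up to about a percentage point.

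| Physiotherapists per arm per site | ICC 0 | ICC 0.01 | ICC 0.05 |
|---|---|---|---|
| 1 | about 5% | 6–7% | 12–13% |
| 2 | about 5% | about 6% | 8–9% |
| 3 | about 5% | 5–5.5% | about 7% |

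With k = 1 and ICC 0.05, the mean model SE was 0.35 against a true SD of the estimate of about 0.44, and CI coverage was about 87%.

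**5. Offset from baseline adjustment.** With baseline correlation ρ, the individual-level part of the variance becomes (1 − ρ² − ICC) × SD² × (1/79.3 + 1/128.7); the physiotherapist part is unchanged. For k = 1, an assumed ρ of 0.5 gives power of 90% at ICC 0, 86% at 0.01, 81% at 0.02 and 69% at 0.05. At ρ = 0.3 it gives 84%, 79%, 75% and 64%.

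**The case against.** The strongest reply is that the harm is conditional. A reader might infer that the CI is certainly too narrow, but the documents do not show this: they give no ICC, and at ICC 0 the planned model is correct. There are grounds for expecting a small value. Physiotherapists share one training course and are checked for fidelity, groups roll with changing membership, and the outcome is self-reported months after the sessions and calls end. None of this shows that the ICC is zero. It limits how firmly the size can be stated.

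The number of physiotherapists per site is also unstated, so the one-per-arm figures are a large-cluster case and should not stand alone.

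A reader might also infer that the trial is underpowered and needs more participants. That does not follow, because the sample size takes no credit for baseline adjustment while the model adjusts for baseline. Depending on the correlation, this may recover much or all of the loss. It does nothing for the CI.

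Nor is it right to say that the model treats participants within a centre as independent outright. It includes a centre effect, so independence is assumed given centre.

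Finally, the analysis plan is not shown and could add a term. But the protocol states both the random effect and the sample-size basis, so these are choices made in the document and not matters it leaves open.

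**Conclusion.** The structural point stands with high confidence: physiotherapist and group are nested in arm within site, and a centre intercept cannot carry their variation. The consequence holds to the extent that the ICC exceeds zero. Confidence in its size is medium, because it rests on assumed ICCs up to 0.05 and on one to three physiotherapists per arm per site. Within those assumptions the effect on type I error runs from negligible to more than double the nominal 5%. The analysis model carries the weight of the point; the power statement is secondary and needs qualifying, not a new total.

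**What to change.** - **Model:** add a random site-by-arm effect to the primary and continuous secondary models, or a physiotherapist effect where the logs allow one main physiotherapist to be assigned to each participant. Use a Kenward-Roger or Satterthwaite degrees-of-freedom correction and report the ICC.
- **Sample size section:** state that 80% assumes no physiotherapist or group clustering. Give power over a range of ICCs and physiotherapists per arm, together with the offset expected from baseline adjustment. Leave 260 unchanged.

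**Cost:** protocol and analysis-plan wording, plus linkage of session logs to participants if a physiotherapist effect is used. The article does not say that the logs identify the physiotherapist for each participant, and in rolling groups a participant may meet more than one; site-by-arm is the fallback and needs no linkage. The CI will be somewhat wider. The added variance will be imprecisely estimated from about 16 to 18 site-by-arm cells (8 or 9 sites × 2 arms) and may come out at zero.

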#### Co-interventions

During the course of follow-up, participants may require further interventions as part of their recovery following surgery as per routine NHS practice. Further clinical interventions will be permitted for trial participants without the participant having to withdraw. If a participant receives additional treatment to the trial intervention, the details of the treatment received and the reasons will be collected.

#### Quality assessment

The trial will be monitored and audited in accordance with the current approved protocol (V. 4.0, 17 September 2019), good clinical practice,^24^ relevant regulations and standard operating procedures (SOPs).

All designated physiotherapists who deliver the usual care group exercises will be taught about the standardised control intervention procedures, that is, clarification on the use of exercise diaries and treatment logs which are additional to usual care.

Designated physiotherapists delivering the behaviour change intervention will attend a 1 day, face-to-face course where they will be taught the intervention and processes involved by a member of the PEP-TALK team who developed the intervention (BF, ZH or TS). In addition, to assess the fidelity to the trial intervention, a health psychologist (BF) will undertake a debriefing telephone call with each physiotherapist after they have delivered their first group session. This will allow the trainer to re-enforce any learning required, address any uncertainties and to identify and correct any variation in the treatment protocol. Finally, each physiotherapist who delivers either the PEP-TALK or control group intervention will be monitored during a site visit at their third or fourth intervention session. The PEP-TALK intervention physiotherapist will be monitored by a health psychologist (BF) or physiotherapist with expertise in health psychology (ZH). Control group interventions will be monitored by a practicing physiotherapist (TS). Sessions will be monitored against the protocol to determine whether there are issues around fidelity, contamination across groups or adherence/compliance of participants. Where further training is required, this will be instigated following these visits. Further monitoring visits will be coordinated as required.

### Assessments

#### Baseline assessment

Baseline data will be collected prior to randomisation during the preoperative assessment appointment, once consent has been obtained. This will include: gender, age, measured height and weight, CCI, self-reported presence and location of multi-site joint pain, comorbidities determined from the medical notes, AMTS, employment status and occupation (when appropriate). Participants will also complete measures on: physical activity (University of California, Los Angeles (UCLA) Activity Scale)^25^; physical function (Lower Extremity Functional Scale (LEFS)^26^; disease-specific function (Oxford Hip Score^27^ or Oxford Knee Score^28^); pain (numerical rating scale for pain); self-efficacy (Generalised Self-Efficacy Scale^29^); fear of movement or kinesiophobia (Tampa Scale for Kinesiophobia^30^); psychological distress (Hospital Anxiety and Depression Scale (HADS)^31^); HRQoL (EQ-5D-5L^32^) and the health utilisation questionnaire.

Follow-up data will be collected 6 and 12 months post-randomisation. Questionnaires will be sent to participants by post from the trial office and returned using a pre-addressed, prepaid envelope. If participants have not responded within 14 days of posting, the trial team will attempt to telephone the participant on up to two occasions to remind them to complete the questionnaires. If required, a second postage of the questionnaires will be provided if requested by the participant during these follow-up telephone calls. If participants wish not to complete the questionnaires, they will be provided with the opportunity to complete the UCLA Activity Scale and EQ-5D-5L questionnaires over the telephone. If these methods fail, the participant would be categorised as a non-responder for that time point only.

In an effort to find evidence-based techniques to improve retention and recruitment to RCTs, a study within a trial (SWAT) will be undertaken. This will examine whether there is a difference in questionnaire response rate by printing the UCLA Activity Scale on pink rather than white coloured paper at the 6 month time point. Results of this SWAT will be reported separately to the ‘host’ trial.

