### Outcome measures

The data collection schedule is presented in table 2.

**Table 2 T2:** Data collection schedule

Data	Time points and mode of data collection			
	Baseline	Intervention period	Month 6 post-randomisation	Month 12 post-randomisation
	Face-to-face	Face-to-face	Postal	Postal
Age (years)				
Gender				
Weight (kg)				
Height (cm)				
Admission date				
Operative procedure (THR or TKR)				
Site of joint replacement				
Duration of hip or knee symptoms				
Presence and location of multi-joint pain				
ASA grade				
AMTS				
List of medical comorbidities				
Physiotherapist exercise class log				
Patient in-session and home exercise diary				
Behaviour change intervention log (group and telephone) (physiotherapist completed)				
Charlson Comorbidity Score				
Employment status and current occupation (when appropriate)				
UCLA Activity Score				
Lower Extremity Functional Scale				
Oxford Hip or Knee Score				
Numerical Rating Scale – Pain				
Generalised Self-Efficacy Scale				
Tampa Scale for Kinesiophobia				
Hospital Anxiety and Depression Scale				
EQ-5D-5L				
Health economic/health utilisation questionnaire				
Complications and adverse events				

Shaded areas represent where these data are being collected.

Assessment intervals following randomisation; each follow-up interval ±1 month.

AMTS, Abbreviated Mental Test Score; ASA, American Society of Anesthesiologists classification; cm, centimetres; kg, kilograms; THR, total hip replacement; TKR, total knee replacement; UCLA, University of California, Los Angeles.

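### A second 12-month questionnaire is posted only on request during a reminder call, so participants reached by neither call get no further prompt: a minor weakness, cheap to fix

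*Protocol article*

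**What the plan says.** The follow-up procedure is described in the Protocol article under Assessments, Baseline assessment. It has five steps, used at both 6 and 12 months.

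1. First mailing: "Questionnaires will be sent to participants by post from the trial office and returned using a pre-addressed, prepaid envelope".
2. If there is no reply within 14 days: "the trial team will attempt to telephone the participant on up to two occasions to remind them to complete the questionnaires".
3. Second mailing: "a second postage of the questionnaires will be provided if requested by the participant during these follow-up telephone calls".
4. For those who do not wish to complete the questionnaires: "they will be provided with the opportunity to complete the UCLA Activity Scale and EQ-5D-5L questionnaires over the telephone".
5. Otherwise: "If these methods fail, the participant would be categorised as a non-responder for that time point only".

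Table 2 (Outcome measures) lists the 6- and 12-month collection as postal, and its footnote sets the window: "Assessment intervals following randomisation; each follow-up interval ±1 month". The Sample size section plans for 80% power "allowing for 20% loss to follow-up".

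**The concern.** Steps 3 and 4 are the only routes by which a non-replier can receive a new form or give the UCLA score another way, and both begin with an answered telephone call. Step 3 also needs the participant to ask. Someone who is away, in hospital, at work or not answering unknown numbers on two occasions is offered neither. The article describes no further contact with that person before classifying them as a non-responder.

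What is at stake is the 12-month UCLA score itself. It is self-reported, and Table 2 shows no 12-month clinic visit at which it could be picked up. The sample size has little slack beyond 20% loss, so obtainable scores are worth pursuing. This is a rule that the article states, not a detail it has left to the full protocol.

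**Working it through.** **Inputs.** From Sample size: standardised effect 0.4 (difference 1, SD 2.5), two-sided 5%, 80% power, 20% loss, 250 participants raised to 260. From Randomisation: 1:1 for 75 participants, then 2:1, with an expected final ratio of about 1.5:1. The documents give no response rate, telephone contact rate or yield from remailing.

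**The plan's own figure.** A two-sample t-test with d = 0.4, 5% two-sided and 80% power needs 99.08 per arm, so 100 per arm and 200 in total; 200 / 0.80 = 250. The normal approximation gives 99 per arm, and 198 / 0.80 = 247.5, so 248. The stated 250 reproduces. At 1.5:1 the normal approximation needs 82 controls and 205 in total; 205 / 0.80 = 256.25, consistent with 260.

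**Slack.** 260 × 0.20 = 52 lost, 208 analysed. The non-centrality is d × √(n₁n₂/(n₁+n₂)). At 1.5:1:

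| Analysed | Split | Non-centrality | Power (t-test) |
|---|---|---|---|
| 208 | 83.2 / 124.8 | 0.4 × √49.92 = 2.826 | 80.3% |
| 214 | 85.6 / 128.4 | 0.4 × √51.36 = 2.867 | 81.4% |
| 221 | 88.4 / 132.6 | 0.4 × √53.04 = 2.913 | 82.6% |

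The second and third rows assume that 12% or 25% of the 52 losses are recovered: 52 × 0.12 = 6.2, about 6, and 52 × 0.25 = 13. Missingness would then be 46/260 = 17.7% or 39/260 = 15.0%. These recovery rates are assumptions. They are optimistic, because the 52 include deaths and withdrawals, and they combine both changes proposed under the fix.

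If 75 are randomised 1:1 and 185 at 2:1, the expected split is 37.5 + 185 × 2/3 = 160.8 to 99.2, a ratio of 1.62. Power with 208 analysed is then 79.6% (t-test) or 80.0% (normal approximation). At 25% loss it is 77.0% or 77.4%.

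**The second mailing on its own.** Let r be the response to the first mailing, c the chance of contact in two calls and s the chance that a person contacted gives data. All three are assumed.

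- Loss as written = (1 − r)(1 − c·s).
- Never reached = 260(1 − r)(1 − c).

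With r = 0.70, c = 0.50 and s = 0.70:

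- Loss = 0.30 × 0.65 = 19.5%, close to the planned 20%.
- Never reached = 260 × 0.30 × 0.50 = 39.
- If an automatic mailing recovers 10% to 30% of the 39 (3.9 to 11.7 people), loss falls to between 18.0% and 15.0%.
- Power (normal approximation, ratio 1.62) rises from 80.3% to between 81.0% and 82.3%.

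With r from 0.60 to 0.80, c from 0.40 to 0.70 and s = 0.70, loss as written runs from 10.2% to 28.8%, and 16 to 62 people are never reached. At the favourable corner the mailing moves power from 84.4% to between 84.6% and 85.1%. At the unfavourable corner it moves it from 75.3% to between 76.7% and 79.2%. The unfavourable corner requires more loss than the plan allows, and nothing in the documents points to that.

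**The case against.** A reader might infer more from this rule than the text supports, in four ways.

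- **That anyone missed in two calls is automatically missing.** Not so. The first form and its prepaid envelope remain with the participant, and a return within the ±1 month window still counts.
- **That a participant who promises to reply and does not is abandoned.** The text allows up to two calls and does not say that calling stops after the first contact. Such a person can be called again, and can then ask for a new form or give UCLA by telephone.
- **That telephone rescue is ill-suited to these patients.** People without access to a working telephone are excluded (Trial participants). That does not guarantee an answer, but the route fits the enrolled population.
- **That the result will be biased.** Being hard to reach may well relate to illness, work or activity, but the documents offer no evidence of this and none of differential loss by arm. The Statistical analysis section adjusts for baseline activity, uses the 6-month data, and provides for multiple imputation if appropriate and for sensitivity analyses on missing data.

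It is also fair to say that post, two calls, a pack on request and telephone capture of the primary outcome already make a multi-step procedure, that the 20% allowance already anticipates loss, and that the size of any gain is assumed.

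What stands after this is narrower. For someone whom neither call reaches, the stated procedure provides no further prompt. Imputation and adjustment reduce the consequence of a missing score, but they do not replace one that could have been collected.

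**Conclusion.** The point holds as a minor improvement to retention. The plan contains no contradiction or arithmetic error here, and its sample size reproduces. The weakness is that the second mailing and telephone UCLA both depend on an answered call, which leaves one identifiable group with a single mailing and no further prompt.

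The likely gain is about 1 to 2 percentage points of power if loss is near the planned 20%. That rests on assumed recovery of 6 to 13 participants, which is an upper range. The documents do not show that loss will exceed 20%, nor that those lost differ from those retained.

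**What to change.** In the follow-up text under Baseline assessment, replace the on-request condition. Post a second questionnaire once to every participant with no return after the reminder step, whether or not a call was answered, unless the participant has declined, withdrawn or died. Timing needs care. If the first form goes out at exactly 12 months, the 14-day wait uses about half of the month that remains in the window, so the reminder calls and second posting must follow promptly, or the first form must go out earlier within the window.

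Optionally, offer telephone UCLA at any successful reminder call and not only to those who do not wish to complete the form. Telephone completion is already permitted, so this adds no new mode. Record the mode of completion for each score.

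The cost is postage for some tens of extra packs, a few minutes per call if the optional step is taken, and a minor amendment. The downside is a second mailing to some people who had silently chosen not to reply. Eligibility, randomisation, treatment and the analysis model are unchanged. The Trial status section expects final follow-up by April 2021, so 12-month mailings not yet sent at the time of an amendment could benefit.
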